# **Data Ownership**

All research data collected during this trial is governed and handled following the Research Data Governance and Materials Handling [policy](https://www.gs.unsw.edu.au/policy/documents/researchdatagovernancepolicy.pdf). UNSW, rather than any individual or Organisational Unit, is the Custodian of data and materials and any information derived from the data. Original research data and primary materials generated in the research conducted at the University will be owned and retained by the University subject to any contractual, statutory, ethical, or funding body requirements.

# **Handling and Reporting Data**

Principal Investigators are responsible for maintaining adequate and accurate source documents and trial records that include all pertinent observations on each site's trial subjects. Source data must be attributable, legible, contemporaneous, original, accurate, and complete.

Trial subjects will be assigned a participant ID, and data will be reported using the case report form (see Appendix B). Data reported on the case report form, derived from source documents, should be consistent with the source documents, or the discrepancies must be explained. Any change or correction to a case report form should be dated, initialled, and explained (if necessary) and should not obscure the original entry (i.e., an audit trail should be maintained); this applies to both written and electronic changes or corrections.

Direct Access to Source Data and Documents

Principal investigator(s) and institution(s) will permit trial-related monitoring, audits, IRB/IEC review, and regulatory inspection(s), providing direct access to source data/documents.

Monitoring Quality Control and Quality Assurance

The Coordinating Principal Investigator and Principal Investigator(s) 'responsibility are to monitor the clinical trial. The Coordinating Principal Investigator and Principal Investigator(s) are responsible for undertaking or participating in site initiation or protocol-specific training before recruitment and data collection commences. A monitoring report demonstrating regular compliance monitoring with the clinical trial protocol, procedures, and HREC approval is provided to the UNSW Sponsor's Delegate annually.

Root, cause, analysis reports are to be completed by the Coordinating Principal Investigator for reports of non-compliance and serious breaches. A corrective and preventative action plan must be developed and actioned for any reports of non-compliance and serious breaches.

# **Essential Documents for the Conduct of a Clinical Trial**

All essential documents referred to in section 8.2 of the [Guideline for Good Clinical Practice (E6, R2)](https://database.ich.org/sites/default/files/E6_R2_Addendum.pdf)   are to be retained by all trial investigators.

# **Data and Safety Monitoring Board Charter**

A randomised controlled trial of an m-health app and digital engagement strategy for improving treatment adherence and reducing suicidal ideation.

| Sponsor: | University of New South Wales, Sydney |
| --- | --- |
| HREC Reference number: | HC210400 |
| BDI Study Identification Number: | 247 |
| Clinical Trials Registration Number: | ACTRN12621001247864 |
| Number of Sites: | One (Australia) |
| Number of Participants: | 669 |

**Data and Safety Monitoring Board (DSMB) Overview**

**DSMB Description**

This DSMB members will have a degree of independence from the Black Dog Institute, University of New South Wales Sydney, and investigators, as required by the NHMRC for non-commercial trials.

This charter will be approved by its DSMB members.

The DSMB will function in accordance with the principles of the following documents: Good Clinical Practice (GCP) Guidelines, Declaration of Helsinki 2000, NHMRC National Statement on Ethical Conduct in Human Research, NHMRC Guidance Safety and Monitoring of Clinical Trials involving a Therapeutic Good, and University of New South Wales HREC guidelines.

**DSMB Membership Conflicts of Interest & Composition**

Members will disclose conflicts of interest and will be cleared of significant conflicts of interest and potential conflicts of interest. No member should have financial, proprietary, professional, or other interests that may affect impartial, independent decision-making by the DSMB.

Composition of membership will reflect expertise in clinical trials (including a good understanding of the problems and limitations of trials), statistics and the specific scientific expertise relevant to the study, in this case, the suicidality in young people. Members will comprise 3 individuals with expertise in these areas.

A quorum group of two must be present for closed sessions and subsequent decisions and/or recommendations made by the committee.

**Reporting**

Data requiring review by the DSMB will be provided by the Trial Manager ([name]) for the open session, and the data officer (TBC) for the closed session.

Issues and recommendations identified by the DSMB will be provided to Trial Steering Group (TSG, Appendix L), comprising the Trial Lead and Chief Investigator ([name]), the Trial co-lead and Investigator/Trial Manager ([name]), and the co-Investigators ([name], [name], [name], and [name]) by the DSMB in accordance with this charter.

**Study Summary**

Involving young people aged 17 – 24 years from the general community in Australia, this randomised controlled trial (RCT) will examine the use of a smartphone application – LifeBuoy - to reduce symptom severity of suicidal ideation. Concurrently, this study also examines whether a digital engagement strategy promotes greater use of the Lifebuoy app. This study will rely on self-report data to evaluate the efficacy of the app, and on automated system data to evaluate the efficacy of the digital engagement strategies. This study is funded by Australian Rotary Health, the Roth Family Foundation, the Mantana Foundation for Young People, and the Goodman Foundation.

**Design**

A double-blind, randomised-controlled trial with three-parallel arms (an intervention arm, intervention + engagement strategy arm, and an attentional control arm) with 1:1:1 allocation. Assessment and study procedures are automated and so the risk of differential treatment of those in the intervention and control is minimised.

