# **Trial Design**

This parallel design randomised controlled trial will involve three arms to answer the main objectives outlined in Section 4: 1) attentional control, 2) LifeBuoy only, and 3) LifeBuoy + engagement strategy. Participants will be followed up over four time-points: 0-days (baseline, T0), (0 days), 1-month (30- days (T1), 2-months (60- days (T2), and 4-months (120-days (T3).

The primary endpoint is change in suicidal ideation at T1 (day-30) relative to T0 (baseline, day-0).

The secondary endpoint is adherence to the LifeBuoy app across time, defined as the number of modules completed by participants at the T1, T2, and T3 post-baseline time-points. Participant module access and module completion data will be automatically collected via the LifeBuoy app.

The following flow chart (Figure 1) describes how an individual participant will progress through the phases of the research process:

[figure not shown]

*Figure 1: Study Process Flow*

Randomisation to treatment arms will occur on a 1:1:1 ratio using a block design using an automated web-based platform tailored for this project. All study assessments will be via electronic self-report. There are no outcome assessors.

Participants will have until the end of the 120-day period to access the apps. They will be prospectively followed up over four time-points: 0-days (baseline, T0), (0 days), 30- days (T1), 60- days (T2), and 120-days post baseline (T3). After completion of the T1 assessment, participants from the LifeBuoy (n=20) and LifeBuoy + engagement strategy (n=20) conditions will be invited to participate in a qualitative interview about the acceptability of the app and engagement strategy (n=40 in total). Participants will be recruited on a first-in first-served basis, and interviews will be conducted within 1-month of completing the T1 assessment to minimise memory failure relating to the engagement strategies.

The discontinuation criteria for individual participants will include if they experience a serious adverse event (Section 9.6 details withdrawal procedures).

The following accountability procedures for the intervention and control apps will apply:

- Software version control ensuring only approved/tested version of each intervention is used in the trial.

Randomization codes will be generated and retained automatically by the Black Dog Institute’s research engine.

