Responsibility for holding and securing the randomisation list and performing any code break will be assigned in the Delegations Log. The list holder cannot be the Principal Investigator, or any other staff member involved in:

- day-to-day trial operations; or
- primary data analysis.

Because individual participants will be aware of, and able to disclose, the intervention to which they were allocated, codes may be broken only in the following situations:

- On completion of the primary data analysis, certified as complete by the Principal Investigator; or
- If required by the trial Data Safety Monitoring Board (see section 13, Ethics) in writing to the Principal Investigator.

Any code break shall be recorded in the Safety Monitoring Register and reported to the Sponsor).

Serious adverse events will be reported into the Data Monitoring Safety Board (DSMB, see Appendix). The trial manager will record the number of notifications at each assessment in the Report for DSMB document and will notify the DSMB every 3-months on how many alerts were triggered, and what follow-up was carried out. They will record these in a Case Report spreadsheet which will be securely stored on the UNSW server.

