**Screening eligibility survey**

Hi, and thanks for your interest in our study! To get started, we just need to ask you a few questions to see if you are eligible to participate. The questions should only take 1 to 2 minutes, and all your answers are confidential.

| What the participant will see | | Drop down response options available |
| --- | --- | --- |
| How old are you? | --- select --- | under 17 years (0)  17 years (1)  18-24 years (1)  25 years or older (0) |
| Are you currently living in Australia? | --- select --- | No (0)  Yes (1) |
| Will you be living in Australia for the next 6 months? | --- select --- | No (0)  Yes (1) |
| Are you fluent in English? | --- select --- | No (0)  Yes (1) |
| Do you own or have access to a smartphone (iOS or Android)? | --- select --- | No (0)  Yes (1) |
| Have you experienced suicidal thoughts in the past 1-month (these can include passive thoughts e.g., “I wish I was dead”)? | --- select --- | No (0)  Yes (1) |
| Have you seen a mental health professional for a mental health concern in the past 6 months? | --- select --- | No (0)  Yes (0) |
| Have been diagnosed with psychosis or bipolar disorder in the past 30 days? | --- select --- | No (1)  Yes (0) |
| **Scoring**: sum 8 items. Eligible if score = 7 only. | | |

(if participant selects age 17 years)

| What the participant will see | | Drop down response options available |
| --- | --- | --- |
| What is this study about? | --- select --- | To find out if a mental health app - LifeBuoy - is effective in helping young people manage their suicidal thoughts (1)  Evaluating if an online game can prevent metal disorder (0)  I have no idea (0) |
| How old do you have to be to participate in this study? | --- select --- | Any age (0)  17-24 (1)  I don’t know (0) |
| What does the study involve? | --- select --- | I will be allocated to one of three groups (intervention app, intervention app + engagement, or control app), use the app I am allocated, and complete four questionnaires over 4-months (1)  I will need to complete a series of online questionnaires to win an Apple iPhone 12 Pro (0)  I don’t know (0) |
| How many questionnaires will you be asked to complete? | --- select --- | Four (1)  One (0)  I don’t know (0) |
| Do you feel pressured to participate in this study? | --- select --- | Yes (0)  No (1)  I’m not sure (0) |
| **Sum the five items.** If total score = 5 then they are eligible. If total ≠ 5 then ineligible. | | |

(If eligible)

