| Health problems (e.g., diseases, chronic sufferings) | 0 | 1 | 2 | 3 | 4 |
| Financial restrictions (e.g. low income, installments) | 0 | 1 | 2 | 3 | 4 |
| Dissatisfaction with education/occupation (e.g. examinations, work overload) | 0 | 1 | 2 | 3 | 4 |
| Difficulties with (secondary) employment (e.g. compatibility with school/college, high responsibility, noise pollution) | 0 | 1 | 2 | 3 | 4 |
| Dissatisfaction with housing situation (e.g., noise, small flat) | 0 | 1 | 2 | 3 | 4 |
| Frequent contradictions, conflicts, tensions with: | | | | | |
| Close friends or family (e.g., family, household, friends) | 0 | 1 | 2 | 3 | 4 |
| Romantic partner (e.g., someone you’re dating, in a romantic relationship with, or married to) | 0 | 1 | 2 | 3 | 4 |
| Other persons (e.g., colleagues, fellow - students, neighbors, tenants, landlords) | 0 | 1 | 2 | 3 | 4 |
| Another burden/stressor not yet mentioned | 0 | 1 | 2 | 3 | 4 |
| **Scoring:** add total (range from 0 to 44) | | | | | |

[Expected app use and motivation] (Use_Exp)

| What the participant will see | | Drop down response options available |
| --- | --- | --- |
| How satisfied have you been with face-to-face treatment overall |  | N/A (0)  Very satisfied (5)  Satisfied (4)  Neither satisfied nor dissatisfied (3)  Dissatisfied (2)  Very dissatisfied (1) |
|  | --- select ---- |  |
|  |  |  |
| Are you looking for alternative mental health treatment to face-to-face therapy? | --- select ---- | No (0)  Yes (1) |
| (If yes) Why? | (free text) | Participant to type in a response |
| If you are currently in face-to-face treatment, how are you expecting to use this app? | --- select all that apply ---- | N/A (0)  To fill a gap between sessions (1)  During face-to-face sessions (2)  To draw out time between face-to-face sessions (3)  When I cannot access my therapist (4)  Other <free text> |
| What motivated you to participate in this study? | (free text) | Participant to type in a response |

[Mobile Application Rating Scale - user version] (uMARS) – T1/30-day assessment only

| We'd like to see what you thought about LifeBuoy. This will help us improve the app. Please select the answer that most accurately represents the quality of the LifeBuoy app.  [quality ratings] | | Drop down response options available |
| --- | --- | --- |

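### The DSMB charter calls the trial double-blind, but participants know their allocation and score the primary endpoint themselves, and the charter does not secure blinding of the trial team either

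*Protocol*

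**What the plan says.** The label stands in the Design section of the DSMB charter: "A double-blind, randomised-controlled trial with three-parallel arms". The only support given there is that procedures are automated, which is said to limit different handling of the arms.

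The protocol's Trial Design section says otherwise about participants. Its code-break rules open with "Because individual participants will be aware of, and able to disclose, the intervention to which they were allocated". The same section defines the endpoint, "The primary endpoint is change in suicidal ideation at T1 (day-30) relative to T0 (baseline, day-0", and says how it is measured: "All study assessments will be via electronic self-report. There are no outcome assessors". The charter's Study Summary agrees: "This study will rely on self-report data to evaluate the efficacy of the app".

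The document says several things about the trial team:

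- **Trial Design** keeps the randomisation list from the Principal Investigator, from staff running the trial day to day and from the primary analysts. Codes may be broken only after the primary analysis or on the DSMB's written requirement.
- **Responsibilities of the Data Officer** (charter) gives that role the purpose of keeping investigators blind to outcome data.
- **Safety Analyses** (charter) denies the Trial Steering Group unblinded ideation, attempt and non-suicidal self-injury (NSSI) data.
- **Access to unblinded data** (charter) lists the trial leads and trial manager, beside the DSMB, as having access.
- **DSMB Documentation and Communication** (charter) places risk alerts and follow-up data, by group, in open sessions.

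**The concern.** An automated, self-guided app trial whose participants know their arm is a legitimate design. The difficulty is that the charter claims a property the trial lacks for its primary endpoint. When an independent rater scores the outcome, unblinded participants can still be paired with a blinded assessment. Here there is no such rater: the person completing SIDAS, PHQ-9 and GAD-7, and reporting attempts and self-injury, is the person who knows the allocation. A SIDAS difference could then reflect expectation or disappointment as well as a change in ideation, and a reader told that the trial was double-blind would not allow for that.

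The other half of the label matters too. If the people who lead and run the trial can see outcome-related data by arm while it is under way, investigator blinding cannot be claimed in its place. The DSMB is asked to ratify this charter before recruitment, so its description of the design should be correct.

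**Working it through.** No figure is at issue, and the sample size does not depend on the label. The check sets the sections side by side.

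**1. Are participants blinded?** Charter, Design: double-blind. Protocol, Trial Design: participants know their allocation. Both cannot hold. The second statement is not a stray remark, because it is the stated reason for restricting code breaks.

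**2. Is the primary endpoint assessed blind by anyone else?** Trial Design rules out outcome assessors and makes every study assessment self-report. The assessor is the participant, so from step 1 the assessment is unblinded. The same holds for the other self-reported symptom and event outcomes. Module completion and app usage are logged automatically and fall outside this argument.

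**3. Does automation fill the gap?** It limits how differently staff could handle the arms. It does not act on what participants expect of the app they know they have.

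**4. Are the trial leads and trial manager blinded?**

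- The charter's first Reporting section places them on the Trial Steering Group.
- Safety Analyses bars that group from unblinded ideation, attempt and NSSI data.
- Access to unblinded data lets the same people see unblinded data, although its next sentence stops the DSMB from sharing with the trial team.
- Meeting formats has them attend open sessions, where risk alerts are supplied by group.

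The Flagging procedure in the Risk Management Protocol triggers an alert on SIDAS above 20, a suicide attempt, or NSSI needing medical care. An alert count by group is thus largely a cut-down version of the data that Safety Analyses withholds, which include the percentage above 20 on SIDAS. Alerts are not rare: the Risk Management Protocol reports 259 flagged among the 455 who completed baseline in the earlier trial, and 259/455 = 57%.

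**5. The T1 app-rating questionnaire (secondary).** The uMARS stem reads "We'd like to see what you thought about LifeBuoy". The block is restricted by time point only, whereas the engagement-strategy block is marked for one arm. As printed, nothing stops it being shown to control participants.

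**The case against.** The strongest reply is that this is one word in an appendix. In the text available, without title and consent pages, the label appears only in the charter. The Trial Design section does not use it and states openly that participants know their arm. DSMB members must also understand the protocol, so they would meet the correct statement. This is fair, and it makes the point one of wording and data flow. It does not remove the contradiction. On team access, by group could mean masked group labels, but the charter does not say so, and that reading would not explain the access granted to the trial leads and trial manager.

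Several stronger readings are tempting, but the documents do not support them:

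- **That the plan claims SIDAS is protected from expectancy bias.** No section says so. The charter speaks only of automation and the handling of the arms.
- **That nothing guards against expectancy.** The objectives specify an attention-placebo control, which may reduce differences in expectation. What control participants are told about their app is not shown.
- **That the competency task reveals allocation.** Its item "I will be allocated to one of three groups (intervention app, intervention app + engagement, or control app" goes only to 17-year-olds and comes before randomisation. It lists the possible arms and discloses nobody's.
- **That the weekly emails unblind the primary contrast.** They separate the two LifeBuoy arms, which the primary SIDAS comparison pools. They bear mainly on the secondary comparison between those arms.
- **That the uMARS wording contaminates the primary score.** SIDAS already comes before uMARS in the printed survey, and a routing rule may exist that is not printed.
- **That the bias can be expressed as a share of the planned d = 0.45.** Any such share would rest on a guessed bias, and it would have no meaning for attempts and self-injury, which are counts.

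**Conclusion.** The point holds as a contradiction about blinding. The charter's label is wrong for participants and therefore for the assessment of SIDAS and every other self-reported outcome. The label cannot be rescued by saying that the investigators are blind, because the charter's own sections conflict on that.

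The size of any bias cannot be derived from the documents, and none is asserted. The consequence is for interpretation: a SIDAS difference is an unblinded self-report effect against an attention control. The conclusion takes the statement on participant awareness in Trial Design at face value. The part on risk alerts assumes that by group means identifiable arms; if labels are masked that part weakens, but the conflict between Safety Analyses and Access to unblinded data remains. The correction should be made, and it changes no sample size or symptom measure. The uMARS point is minor.

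**What to change.** 1. In the charter's Design section, replace the label with a statement that participants are not blinded and that they report the symptom outcomes themselves.
2. State that the SIDAS effect will be interpreted as an unblinded self-report effect against an attention control.
3. Reconcile Safety Analyses, DSMB Documentation and Communication, and Access to unblinded data, so that outcome and alert data by group go only to the DSMB and the data officer. Open sessions would receive alert counts pooled over arms.
4. Only after step 3, state that investigators and analysts are blinded until the primary analysis is complete. This agrees with the code-break rules in Trial Design. Making the statement while the access conflict stands would replace one contradicted claim with another.
5. In the T1 survey, either limit uMARS to the two LifeBuoy arms or reword its stem to refer to the app the participant was given. Leave SIDAS ahead of it, as now printed.

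The cost is charter wording, one survey setting, and moving by-group alerts from the open to the closed report. The design is described less favourably, and the trial leads and trial manager lose access to by-group data. The flagging procedure works on individual responses and makes no reference to arm, so it is not affected.
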